# Selection and Enrollment of Subjects

## 4.1. Inclusion and Exclusion Criteria

The inclusion criteria are as follows and will be determined by an online self-reported screening survey.

Participants will be deemed **eligible** if they:

- Are 16 to 25 years old (inclusive)
- Are living in Australia
- Are fluent in English
- Own and have access to a smartphone
- Experienced mild to moderate suicidal thoughts in the past year (SIDAS scores < 21).

Participants will be **ineligible** if they:

- Have ever been diagnosed with psychosis or bipolar disorder
- Have made a suicide attempt in past month.

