## 4.4. Condition Allocation

After screening and registration is complete, participants will be asked to complete the baseline assessment – which is also delivered online, via the trial portal (website). Upon completion of the baseline survey, they will be automatedly randomised to a condition via an algorithm built into the Research Engine trial software. Subjects are not informed of which condition they have been allocated to. The two applications both have LifeBuoy in their title and look the same, only the content differs.

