**Table. Overview of Survey Schedule**

| Measure | **Outcome** | **Screening** | **Pre** | **Post** | **4-month** |
| --- | --- | --- | --- | --- | --- |
| Demographics | Demographics | - | X | - | - |
| SIDAS | Suicidal ideation | - | X | X | X |
| PHQ-9 | Depression, suicide attempt | - | X | X | X |
| GAD-7 | Anxiety | - | X | X | X |
| DQ-5 | Psychological Distress | - | X | X | X |
| SGS | Suicide Cognitions | - | X | X | X |
| RTQ-10 | Rumination | - | X | X | X |
| ISI | Insomnia | - | X | X | X |
| SWEMWBS | General mental wellbeing | - | X | X | X |
| DTS | Distress tolerance | - | X | X | X |
| TILS | Loneliness | - | X | X | X |
| GHSQ | Help-seeking intention | - | X | X | X |
| Modified-CSRI | Actual help- seeking | - | X | - | X |
| Modified-NLESS | Negative life events | - | X | - | - |
| SGS | Grit | - | X |  |  |
| Expectations of Success | Expectations of Success | - | X | - | - |
| Satisfaction with app | Satisfaction | - | - | X | - |

Participants in both conditions will be reimbursed for undertaking the post-intervention(T1) and 4-month post-intervention (T2) follow up surveys to reduce attrition at these timepoints. Participants will receive a $20 e-giftcards (from GiftPay; see <https://www.giftpay.com.au/business/egifts.aspx>.) at each of these two timepoints, providing a total reimbursement of $40 per participant if they undertake both surveys.

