# Appendix A: Recruitment materials

**The LifeBuoy App: A randomised controlled trial of a mHealth intervention to help young people manage suicidal thoughts**

We are looking for young people who have experienced suicidal thoughts to participate in a study evaluating the effectiveness of a smartphone app “LifeBuoy” that is designed to reduce suicidal thoughts.

We need young people who:

- Are 16-25 years old;
- Are living in Australia;
- Are fluent in English;
- Own and have access to a smartphone;
- Have experienced suicidal thoughts in the past year;
- Have not been diagnosed with psychosis or a bipolar disorder;
- Have no suicidal attempt or plan in the past month.

Eligible participants will:

1. Be assigned to one of two groups: an intervention group (who receives the therapeutic app) or a control group (who receives a non-therapeutic app). All participants will then follow the same process;
2. Complete 7 modules in the app over 6 weeks (total 1 hour);
3. Complete an online survey on 3 occasions: before (35 minutes) and after completing all modules (25 minutes), and then 3 months after the completion of all modules (25 minutes). The survey will include questions about your demographics, suicidal thoughts and suicide attempts, negative life events, how you have been feeling lately, sleep, help-seeking intentions and experience, perseverance, and expectations of and satisfaction with the app;
4. Download an app called ‘Lifebuoy’ after completing the first survey, (you will not know whether you are receiving the intervention or control version of this app). Both apps will be available for 6 weeks for use on your personal smartphone. If you receive the control app, you will be informed after the final survey to let you know that you were in the control condition, and what that means.
5. Receive a $20 gift card in acknowledgement of your time and internet expenses related to participation in each follow-up survey (total $40 gift card if you complete both follow-up surveys).

Please note: suicide related questions will be asked in the online survey. Participants are free to withdraw at any time. The identified information obtained in this study will remain confidential and be stored in an archive on the UNSW server hard drive for a period of 7 years.

If you are interested in participating this study, please click here <Insert link: XXX>.

This study has been approved by Human Review Ethics Committee at the University of New South Wales [HC190764]

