**Advertisement for social media channels**

The Black Dog Institute is inviting young people aged 18-25 who have experienced suicidal thoughts to participate in a study evaluating the effectiveness of a smartphone app designed to reduce suicidal thoughts. You will receive $40 in appreciation for your time in participating. This study involves the completion of 7 app modules over 6 weeks (1 hour total), and one online survey before starting the app (35 minutes) and two surveys after (immediately and 3-months later; 25 minutes each).

Click here <Insert the link to the recruitment page> to get more information. Lifeline: [name].

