# Appendix B: Screening and Eligibility

**Screening questions**

| **What the participant will see** | | **Drop down response options available** |
| --- | --- | --- |
| Are you aged between 16 and 25? | --- select --- | Yes, I’m between 16 and 20 years old  Yes, I’m between 21 and 25 years old  No |
| Are you living in Australia currently? | --- select --- | Yes  No |
| Are you fluent in English? | --- select --- | Yes  No |
| Do you own, or have access to, a smartphone (iOS or Android)? | -- select --- | Yes  No |
| Have you experienced suicidal thoughts in the past 12 months? | -- select --- | Yes  No |
| Have you attempted suicide in the past month? | -- select --- | Yes  No |
| Have you ever been diagnosed with psychosis or bipolar disorder? | -- select --- | Yes  No |
| Gender assigned at birth | -- select --- | Male  Female |

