**Study Summary**

Involving young people aged 18 – 25 years from the Australian general community, this randomised controlled trial (RCT) will examine the use of a smartphone application (‘LifeBuoy’) to deliver digital Dialectical Behaviour Therapy (DBT) and Acceptance and Commitment Therapy (ACT) to reduce symptom severity of suicidal ideation. This study will rely on self-report data to evaluate the efficacy of the app. This study is funded by the Roth Family Foundation and an Australian Rotary Health Youth Mental Health Grant for 2 years.

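### Section 4.1 limits entry to SIDAS below 21, but no step described in the protocol applies that limit before automatic randomisation

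*Protocol*

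**What the plan says.** Section 4.1 of the protocol states: "The inclusion criteria are as follows and will be determined by an online self-reported screening survey". One of those criteria is "Experienced mild to moderate suicidal thoughts in the past year (SIDAS scores < 21".

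The screener printed in Appendix B covers ideation with a single Yes/No item: "Have you experienced suicidal thoughts in the past 12 months". Section 4.3 describes the screening content in the same terms, as the presence of suicidal thoughts and attempts. People who pass are registered automatically and go on to the baseline survey. The schedule table in Section 6.5 (columns Screening, Pre, Post, 4-month) has the row "SIDAS | Suicidal ideation | - | X | X | X". Section 4.4 then says: "Upon completion of the baseline survey, they will be automatedly randomised to a condition".

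Elsewhere the same cut on SIDAS serves safety only. A score above 20 is an expected adverse event (Section 10.1), triggers contact at the three-week check (Section 12.1), is a listed safety analysis, and defines the at-risk flag in the stopping guidelines (both Appendix E).

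Other entry limits also differ within the current text. The social media advertisement in Appendix A is "inviting young people aged 18-25 who have experienced suicidal thoughts", and the charter summary in Appendix E begins "Involving young people aged 18 – 25 years from the Australian general community", while Sections 3.3 and 4.1 give 16 to 25. The main recruitment text in Appendix A adds "Have no suicidal attempt or plan in the past month"; Section 4.1 excludes only a recent attempt.

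**The concern.** The protocol fixes an entry rule and also fixes a screening instrument that cannot evaluate it. If the text is followed literally, nothing stops a person scoring 21 or more from being randomised.

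Three things are at stake.

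- **Population.** Sections 4.1 and 5.1 describe a mild-to-moderate group. Results could be reported for a population that was never selected on severity.
- **Safety reading.** Someone above the limit at baseline is already over the SIDAS > 20 line before using either app. None of the passages using that line says whether a baseline score counts.
- **Conduct.** Section 11.1 treats including a person who does not meet the criteria as a protocol deviation, and describes deviations as neither persistent nor systematic. An entry route with no check for the criterion would be systematic.

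**Working it through.** **1. The route to randomisation, in order.**

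- Screening (Section 4.3, Appendix B): eight items. Ideation and past-month attempt are each Yes/No. None is a SIDAS item, so no 0 to 50 score exists.
- Registration (Section 4.3): automatic for those who pass.
- Baseline (Section 6.5, Appendix C): SIDAS is answered for the first time.
- Randomisation (Section 4.4): automatic on completing baseline. No score rule is described.
- Three weeks later (Section 12.1): SIDAS safety check, after allocation.

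The limit could act only between baseline and randomisation, and the text describes no check there.

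**2. The entry limit and the safety line are the same cut.** SIDAS is the sum of five whole-number items scored 0 to 10 (Section 6.1), so a score above 20 is a score of 21 or more. Anyone who fails the entry limit is above the safety line on day 0.

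**3. Recall window.** The criterion says past year. Section 6.1 and the Appendix C instructions ask about the past month. The score cannot measure severity over the period that the criterion names.

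**4. Sample size, to see whether the plan's figure is affected.** Inputs from Section 8: d = 0.30, pre-post correlation r = 0.50, power 0.80, alpha 0.05 (two-sided assumed), attrition 30%.

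- n per arm = 2 (1.960 + 0.842)² (1 − r²) / d² = 2 × 7.85 × 0.75 / 0.09 = 130.8, so 131.
- 131 / 0.70 = 187.1, so 188, against 189 stated.
- With 189 × 0.70 = 132.3 completers per arm, power is 0.804.

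The stated figure reproduces and does not depend on where SIDAS is scored.

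**5. Size, under an assumption only.** The protocol gives no baseline SIDAS distribution. Let q be the assumed share of otherwise eligible baseline completers scoring 21 or more. Without a gate, 378 × q of those randomised lie above the limit. With a gate, 378 / (1 − q) baseline completers are needed. Section 4.2 cites 71 baseline completions in one month in an earlier trial; at that rate 378 take 378 / 71 = 5.3 months, against the six stated.

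| q | Above limit among 378 | Completers needed with a gate | Months at 71 per month |
|---|---|---|---|
| 10% | 38 | 420 | 5.9 |
| 20% | 76 | 473 | 6.7 |
| 30% | 113 | 540 | 7.6 |
| 40% | 151 | 630 | 8.9 |
| 50% | 189 | 756 | 10.6 |

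**6. Possible power cost of enforcing the limit.** Assume a normal baseline score and that r = 0.50 refers to the unrestricted population. Cutting off the upper share q leaves baseline variance v = 1 − bλ − λ², with b = Φ⁻¹(1 − q) and λ = φ(b)/(1 − q). The correlation becomes r√v / √(1 − r² + r²v).

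- q = 10%: r = 0.44, 202 per arm needed, power at 189 is 0.775.
- q = 30%: r = 0.38, 215 needed, power 0.749.
- q = 50%: r = 0.33, 223 needed, power 0.734.

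This holds d at 0.30 in the restricted group. If r = 0.50 already describes people below 21, nothing changes. Nor does power fall if the effect in SIDAS points is unchanged, because selecting on baseline leaves the residual variance as it was.

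**7. Other entry limits side by side.**

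- Age 16 to 25: Sections 3.3 and 4.1, the main recruitment text and the short advertisement in Appendix A, and the Appendix B screener. Age 18 to 25: the social media advertisement in Appendix A and the charter summary in Appendix E.
- Recent plan as an exclusion: main recruitment text in Appendix A. Absent from Section 4.1 and the screener.

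**The case against.** A reader might infer that the limit is never applied and that the trial will enrol people outside its population. The documents do not support that. Figure 1, the study flow, is not shown. Section 4.3 says the screening questions align with the criteria and introduces its list with a word that does not make it exhaustive. Section 4.4 is silent on a gate, which does not rule one out. The dash for SIDAS in the schedule is weak evidence, because every measure has a dash in the Screening column. Appendix B places consent after screening while Sections 4.2 and 4.3 place it before, so the printed screener may not be the current one. All of this stands. It limits the claim to what the available text describes, but it does not supply the missing step.

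A reader might also infer that the safety figures shown to the monitoring board are inflated, or that high scorers are left without support. Neither follows. Under Appendix E the board meets after baseline collection and its reports are cumulative, so a baseline rate could be seen and compared, and randomisation balances baseline scorers in expectation. Both apps carry the help button (Sections 5.2 and 12.1), and Section 12.1 adds the three-week check with psychologist contact.

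The age conflict might be put down to the change log. It does not rest on the log: both ranges stand in current text. The screener's 16 to 20 band does fit Section 4.1 as written, so it is not an error in itself.

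**Conclusion.** The contradiction holds. Section 4.1 sets SIDAS below 21 and assigns the decision to a screening survey which, as printed and as described, cannot make it; randomisation then follows baseline automatically. As written, people scoring 21 or more can be randomised, and some may be over the SIDAS > 20 line before any exposure.

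The number is unknown. The counts in the table are consequences of assumed shares, not estimates, and the conclusion does not depend on them. A reader might also infer bias in the primary comparison; there is none from this source, since allocation is random either way, and the planned 189 per arm is unaffected. The damage is to who the results describe and to how the safety line is read.

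The mismatch between past year and past month, the two age ranges and the recent-plan exclusion are separate inconsistencies in the entry criteria, and all stand. The point should be settled before enrolment, because it cannot be undone afterwards.

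**What to change.** Reconcile Sections 3.3, 4.1, 4.3, 4.4 and 10.1 with Appendix B before enrolment, in one of two ways. The choice belongs to the investigators.

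- **Keep the limit.** Score SIDAS before randomisation, either by adding its five items to the screener or by a software rule on the baseline score, and word the criterion on the scale's own recall window. The change itself is small. The cost is more people screened, slower recruitment (on the assumed shares, 420 to 756 baseline completers to randomise 378) and possibly some loss of power from the narrower baseline range.
- **Remove the limit.** Make the population description in Sections 3.3, 4.1 and 5.1 match what the screener selects. This costs only text, but gives up the claim to a mild-to-moderate sample.

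Whichever is chosen, check that the SIDAS > 20 passages in Sections 10.1 and 12.1 and in Appendix E are consistent with it.

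Also settle one age range across Sections 3.3 and 4.1, Appendices A and B and the charter, changing the screener's age bands only if the chosen minimum requires it. State the recent-plan exclusion in all of these places or in none.

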## 4.2. Study Recruitment Procedures

**Trial.** Participants will be recruited into this trial via social media advertisements (e.g. Facebook, Twitter, Instagram, website), which are targeted to the inclusion criteria. Individuals interested in participating will click on the following link, which will be embedded in the advertisements:

https://blackdoginstitute.org.au/lifebuoy_study.

This link will take participants through to the study website hosted on Black Dog Institute’s research engine. Here they will be presented with an online version of the participant information sheet and consent form. Participants will need to consent to participation before being directed on to the eligibility screening survey. This strategy has been successfully used in a recent trial of a relationship app for depression, and 399 eligible participants were recruited and registered in one month. 71 (17.7%) of those recruited completed baseline assessments, indicating that the required sample size for this trial will take six months.

Recruitment wording in described in Appendix A.

**Qualitative Interviews.** For the qualitative interviews conducted at the final (T2) assessment, we will recruit a 10% subsample of individuals who participated in the intervention condition (expected to recruit n=189) to assess their experience with the app. Justification for this sample size is described in Section 8.

Recruitment to the qualitive interviews will take place immediately *before* the final assessment. At the time of the final assessment, but prior to receiving the assessment, participants in the intervention group will be emailed a letter of invitation to participate in the qualitative study, using the details they registered for the trial with. The delivery of this invite will be automated as part of a pre-determined schedule of survey and reminder delivery in the Research Engine.

The wording for the letter of invitation is as follows:

**“Before you start the final assessment, we just want to check if would you be interested in participating in a 30-minute one-on-one telephone or videoconference interview about your experience of using the LifeBuoy app? We are keen to hear from you if you did or did not use the app, to learn why. You will be reimbursed $30 for your time if you chose to participate:**

**Yes**

**No**

If a participant selects 'yes' a message will be displayed saying “**That is great news, we’ll now ask you to read and reply to the Participant Information and Consent Form, and then you can proceed on to the final assessment**”. Once they have read the Participant Information Sheet and completed the online consent, an automated email is sent to the research inbox ([contact]) to notify the research team which participants to schedule an interview with.

If they select ‘no’, a message will be displayed saying “**Thanks for that, you can now proceed to the final assessment”** and will be able to click through to the survey.

As part of the Information Sheet, participants will be informed that they will be selected to participate in an interview on a first come first served basis, in case a large number of people are interested. Participants will be contacted by a research team member, and a date and time will be arranged for a telephone or videoconference interview (whichever they prefer). Participants will be told that if they fail to attend the interview at the designated time without giving prior notice, their place will be given to someone else.

Participants who respond after the first 20 people are confirmed will be informed by email that the quota is full, but they will be placed on a waiting list should some participants not be able to attend the interview. The order of the waiting list is ranked according to the participants’ response date and time, with earlier responses ranked higher on the list.

## 4.3. Consent and Screening

Participants will be provided with the Participant Information Sheet and Consent Form [PISCF] online, once they click on the recruitment advertisement. Participants will be asked to read the PISCF and will have sufficient time to consider their participation because there is no time restriction before they consent and register to participate. Participants will be advised to contact the researcher(s) if they have any questions. The PISCF will be available for participants to download at the time of reading and from the study landing page if they wish. Once they are comfortable providing their consent to participate, participants will be asked to digitally sign the consent form and click ‘submit’, which will all be managed online via the trial portal (hosted on Black Dog Institute’s research engine).

After the completing the consent procedure, potential participants will be automatically directed to complete a brief online survey within the study portal (website) to assess their eligibility for the trial. Individuals will be asked questions that align to the inclusion and exclusion criteria, including their age, whether they are living in Australia, fluency of English, smartphone ownership, previous diagnosis of psychosis or bipolar disorder, presence of suicidal thoughts and attempts. Individuals who are deemed ineligible will be directed to a webpage thanking them for their time. This webpage will include relevant support contact details. The screening questions and eligibility/ineligibility wording is described in Appendix B.

Young people who are eligible will be automatedly directed to register in the study (by providing an email address and mobile phone number), which will allow survey links and reimbursement to be digitally sent to them.

## 4.4. Condition Allocation

After screening and registration is complete, participants will be asked to complete the baseline assessment – which is also delivered online, via the trial portal (website). Upon completion of the baseline survey, they will be automatedly randomised to a condition via an algorithm built into the Research Engine trial software. Subjects are not informed of which condition they have been allocated to. The two applications both have LifeBuoy in their title and look the same, only the content differs.

## 4.5. Withdrawal of Consent or Participant

Participants may be withdrawn from the study if:

- They experience a serious adverse event that:
  - is attributable to a study intervention or procedure; or
  - means they can no longer participate in the study; or
- They withdraw consent to take part.
- We will not be replacing participants that are withdrawn from the study.

The team clinical psychologist will follow-up with subjects withdrawn due to experiencing a serious adverse event that was attributable to the study intervention or procedure. These participants will be contacted via email within 72 hours of withdrawing from the trial with a list of crisis contact numbers for support. In this email, participants will also be asked to respond to the email (by clicking ‘reply’) if they would like to receive a phone call from the team clinical psychologist during business hours (9:00 to 17:00 AEST). If they say yes, they will be contacted within the following 72 hours.

Participants can self-withdraw at any time by submitting to the study team the UNSW standard withdrawal form appended to the Participant Information Statement and Consent Form. No mechanisms for automated withdrawal (e.g. via the study app) will be provided. To ensure that data belonging to a participant who withdraws can be uniquely identified, their mobile number and email address will be solicited on the withdrawal of participation form. Excluding self-withdrawals, the decision to withdraw a participant will be made by the Principal Investigator.

Handling of participant data after withdrawal will depend on when a participant decided to withdraw from the study. Participants will have their data removed from the study if they:

- Withdraw or are withdrawn prior to completion of the baseline assessment. Reflecting the intention-to-treat principles informing the planned analyses of the trial, data from participants who withdraw after this point will not be discarded.

For those who install the app, access the app once, and complete baseline, subsequent non-response (rather than active withdrawal) will not be treated as withdrawal but handled as missing data unless the specifically request to have their data withdrawn.

Non-identifiable data about withdrawals enabling aggregate reporting (e.g. counts by intervention assignment) will be retained in a Withdrawals Log. In addition, any participant withdrawal linked to an adverse event will be recorded to enable reporting of safety-related statistics. Participants who withdraw from the study will not be replaced and will not be followed up except per adverse event follow-up, if applicable.

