# Risk management

## 12.1. Risk mitigation strategies

To minimise known harms, risks, and discomfort to participants, the below procedures will be implemented in the study. In both the control and intervention apps there is a help button that contains a directory of key sources of help such as phone numbers for Kids Helpline and LifeLine to ensure that participants have access to support 24/7. Participants are also reminded of contacting their GPs when feel distressed and maintaining their regular medicine during the trial.

In addition, there is a “get help now [panic button]” under this “help button”. When young people click the “get help now button”, a screen will pop up in the app to seek confirmation that they want to be contacted by a clinical psychologist during business hours. Once confirmed, a text message containing young people’s contact number will be sent to the clinical psychologist. They will be contacted by the clinical psychologist within the next 24 business hours.

In the middle of the trial (3-weeks after baseline assessment), young people will be asked to complete a safety check (approximately 1 minute) to assess their suicidal thoughts (using the SIDAS screener). If they report a SIDAS score above 20 they will be contacted by a clinical psychologist to refer them to appropriate psychological support, if they consent.

In addition, an independent Data Safety and Monitoring Board (DSMB) will be established to monitor the safety of research participants. DSMB membership will consist of 3 external members who are experts in clinical trial conduct, statistics, and youth mental health. The research team will record the number of notifications and notify the DSMB when each assessment period is complete. The DSMB will provide recommendations to the research team to continue, temporarily pause conduct of the trial, or discontinue, pending risk issues or adverse events. The research team will record all risk alerts in a case report which will be securely stored on the Black Dog Institute’s UNSW server.

The DSMB Charter is attached as Appendix E.

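### After withdrawal for a study-attributable serious adverse event, section 4.5 requires no psychologist call unless the participant answers an email, and its clock starts at withdrawal

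*Protocol*

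**What the plan says.** Section 4.5 opens with a general commitment: "The team clinical psychologist will follow-up with subjects withdrawn due to experiencing a serious adverse event that was attributable" to the study intervention or procedure. It gives that commitment two steps.

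- **Email.** "These participants will be contacted via email within 72 hours of withdrawing from the trial with a list of crisis contact numbers for support". The email also asks the participant to reply "if they would like to receive a phone call from the team clinical psychologist during business hours", which the section gives as 9:00 to 17:00.
- **Call.** "If they say yes, they will be contacted within the following 72 hours".

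On who starts the process: "Excluding self-withdrawals, the decision to withdraw a participant will be made by the Principal Investigator". Later in the same section, withdrawn participants "will not be followed up except per adverse event follow-up, if applicable". That exception carries no content, channel or time limit.

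**The concern.** The participants are young people with recent suicidal ideation, and this group has also had a serious event put down to the study. Someone in that position may be unable or unwilling to answer an email. For those not already under care, the only unconditional contact with a stated form and deadline is one message listing crisis numbers. Whether anyone speaks to them depends on their asking.

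This sits awkwardly with the protocol's own rationale. Section 2.1 stresses young people's reluctance to seek help and cites a weighted average of 29.5% seeking or engaging with mental health services among people with past-year suicidal ideation, plans or attempts. That figure is not a reply rate to an email, but it argues against making the safeguard depend on the participant's request.

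The starting point of the clock matters too. The 72 hours begin at withdrawal, which may come some time after the team learns of the event.

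**Working it through.** There is no design figure to reproduce. The check adds the stated limits and then looks for a rule elsewhere that would close the gap.

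**Inputs, all from 4.5:** email limit 72 h after withdrawal; call limit 72 h after a yes reply; reply time *r*, not limited; time *d* from awareness of the event to withdrawal, not limited.

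**Latest compliant times**

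| Contact | From withdrawal | From awareness |
| --- | --- | --- |
| Email | 72 h | *d* + 72 h |
| Call, if the participant replies yes | 72 + *r* + 72 = 144 h + *r* | *d* + 144 h + *r* |
| Call, if there is no reply | none required | none required |

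With an immediate reply (*r* = 0) to an email sent at its limit, the call may come 144 / 24 = 6 days after withdrawal. These are outer limits, not expected times.

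**Does another section require contact in this situation?**

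- **Sections 10.2 and 10.3.** The 24-hour limits are for reports to the Coordinating Principal Investigator and, for SAEs, the data and safety monitoring board (DSMB). Neither is a contact with the participant. Read literally, 10.3 also defines SAEs as events unrelated to the intervention, so it does not clearly cover the attributable events of 4.5.
- **Table 2.** It has no SAE row, and the rows it has concern reporting.
- **Section 11.1.** It mentions urgent safety measures. Nothing there stops staff acting sooner, and nothing requires a call.
- **Section 12.1, help button.** "They will be contacted by the clinical psychologist within the next 24 business hours". The participant has to start this.
- **Section 12.1, 3-week check.** When "they report a SIDAS score above 20 they will be contacted by a clinical psychologist to refer them to appropriate psychological support, if they consent". Here the psychologist makes the contact without a prior request, although the consent clause may qualify the contact or only the referral. The trigger is a score at one check, not withdrawal for an SAE.
- **Appendix E (DSMB charter).** Its 24-hour limits are for notifying the Chair or the DSMB.

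None of these supplies a required call, or a clock starting at awareness, for this group.

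**The case against.** The strongest reply is that this is a clinical-procedure choice and not an error. No other section contradicts 4.5 on this group, and contact by invitation after someone has left a study is defensible. The opening commitment is unconditional and the adverse-event exception is kept, so the email and call can be read as a minimum. SAE handling also follows a flow chart (Figure 2) and institutional guidelines that are not in the text available, so a contact duty there cannot be ruled out. The SAE criteria in 10.3 include hospitalisation and life-threatening events, so many survivors would already be in care. The charter places the trial in its lowest risk category.

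Most of this limits the size of the point. A wider duty may be intended, but 4.5 gives it no form or deadline, and a participant who does not reply is exactly the case it leaves open.

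A reader might also infer more than the documents support:

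- **That a requested call is three times slower than the help-button response (72 / 24 = 3).** The only business hours the protocol defines are 9:00 to 17:00, or 8 hours a day. On that reading 24 business hours is 24 / 8 = 3 working days, and 72 hours is no longer.
- **That 4.5 breaches a 48-hour contact limit.** The charter mentions 48 hours for participants flagged on the SIDAS and attributes it to a Duty of Care section. No such section is in the protocol text, and the figure concerns another group.
- **That 12.1 shows 4.5 to be slow.** For a score above 20, 12.1 states neither a time nor a channel. It supports only the narrower point that the psychologist can be the one to initiate contact.
- **That earlier contact is forbidden, or that withdrawal decisions will be slow.** The text says neither. It only leaves both times unlimited.

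**Conclusion.** The point holds as a minor safety improvement. Section 4.5 promises psychologist follow-up after withdrawal for an attributable SAE, but it fixes only an email within 72 hours of withdrawal and a call on request within a further 72 hours. Someone who does not reply is owed no call, and the time from awareness to withdrawal is not counted.

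In size, the latest call is 144 hours after withdrawal plus reply time, with any delay before withdrawal on top. The protocol gives no expected number of such events, so the number of participants affected cannot be stated. It is probably small.

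The conclusion assumes that the unseen flow chart and guidelines add no duty to contact the participant. If they do, 4.5 needs only a cross-reference. Whether the arrangement is adequate is for the clinical team and the ethics committee to judge. The trial's estimates, tests and sample size are unaffected.

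**What to change.** Amend 4.5 to say that, once the team is aware of an SAE attributable to the study, the team clinical psychologist attempts a call to the participant's registered mobile number without waiting for an email reply, unless the participant has declined further contact. The clinical team should set the time limit, counted from awareness and no longer than the present 72 hours. Keep the email with crisis numbers as an addition.

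The change is confined to 4.5 and uses the psychologist already on the team and the mobile numbers collected at registration. It costs a few extra calls, some to participants already in care. Section 4.3 gives survey links and reimbursement as the reason for collecting contact details, so check that the consent form covers such calls and amend it if not.
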